# Progressive mobility program and technology to increase the level of physical activity and its benefits in respiratory, muscular system, and functionality of ICU patients: study protocol for a randomized controlled trial

**DOI:** 10.1186/s13063-018-2641-4

**Published:** 2018-05-10

**Keywords:** Early mobility, Rehabilitation, Critical care

## Abstract

**Background:**

Enhanced mobility in the Intensive Care Unit (ICU) could minimize the negative effects of critical illness, such as declines in cognitive, muscular, respiratory, and functional capacity. We aim to compare the functional status at ICU discharge of patients who underwent a progressive mobilization protocol versus patients who received conventional physiotherapy. We also examine the level of physical activity in the ICU, the degree of pulmonary and muscle function, and the length of stay to analyze correlations between these variables.

**Methods:**

This is a protocol for a randomized controlled trial with blind evaluation. Ninety-six ICU patients will be recruited from a single center and randomly assigned to a control group or an intervention group. To determine the level of protocol activity the patient will receive, the patients’ ability to participate actively and their muscle strength will be considered. The protocol consists of five phases, ranging from passive therapies to walking and climbing stairs. The primary outcome will be the functional status at ICU discharge, measured with the Barthel Index and the ICU Mobility Scale (IMS). Measured secondary outcomes will include the level of physical activity, maximal inspiratory and expiratory pressures, forced expiratory volume in 1 second, maximum voluntary ventilation, handgrip strength, surface electromyography of the lower limb muscles, and results of the Timed Up and Go and 2-Minute Walk tests. Evaluations will be made within 2 days of ICU discharge except for the level of activity, which will be evaluated daily. Physiological variables and activity level will be analyzed by chi-square and *t* tests, according to the intention-to-treat paradigm.

**Discussion:**

Mobility and exercise in the ICU should be undertaken with intensity, quantity, duration, and frequency adjusted according to the patients’ status. The results of this study may contribute to new knowledge of early mobility in the ICU, activity level, and varying benefits in critical patients, directing new approaches to physiotherapeutic interventions in these patients.

**Trial registration:**

Recruitment will begin in February 2017, and the expected completion date is August 2018. Patients are already being recruited.

ClinicalTrials.gov, ID: NCT02889146. Registered on 3 March 2016.

**Electronic supplementary material:**

The online version of this article (10.1186/s13063-018-2641-4) contains supplementary material, which is available to authorized users.

## Background

A large number of patients who survive hospitalization in the Intensive Care Unit (ICU) experience negative effects of critical illness, even after stabilization of the condition, presenting cognitive, psychological, and physical changes as the main morbidities. In a prospective cohort study of 1075 patients 5 months after discharge, 48% of patients needed help in at least one activity of daily life [1]. Data show that 1 year after their stay in ICU, patients still reported muscle weakness, loss of muscle mass, and fatigue, and half of those patients had not yet returned to occupational tasks [2]. Even after 5 years, some of these changes persisted in most patients [3]. In another study, quality of life was evaluated at 1 year and 4 years after hospital discharge, with results indicating a decrease in quality of life in surviving patients due mainly to a decrease in physical function [4].

These medium and long-term consequences originate at the beginning of hospitalization and are related to changes that occurred during the stay in the ICU. In this period, patients may experience a period of inactivity and prolonged rest resulting in immobility, related to changes in various systems of the body. In the respiratory system, the main consequences of this immobilization are atelectasis, mechanical ventilation (MV), and hospital-associated pneumonia as well as delayed removal of the MV due to muscle weakness, decreased vital capacity, and residual volume [5, 6].

Studies of immobility in bed have shown a decrease in strength and muscle mass with variations similar to the losses experienced during ICU stays, with a decline of 1–1.5% per day and up to 50% of total muscle mass in 2 weeks [5]. In healthy people, immobilization has been shown to induce muscle atrophy, characterized by decreased protein content, fiber diameter, fatigue resistance, and strength [7]. Signs of cardiovascular dysfunction are observable within 3 to 4 days of immobility in the bed [8]. These effects, seen in healthy, bed-restricted patients may be potentially relevant for ICU patients who also present with fluid loss, as evidenced by a decrease in plasma volume of 10–20%. This decrease contributes to postural hypotension and tachycardia as well as decreased systolic volume, ejection volume, cardiac output, and oxygen uptake [9, 10].

In the ICU, in addition to immobility, muscular dysfunction is common due to multiple factors such as inflammation, the use of pharmacological agents (corticosteroids, muscle relaxants, or antibiotics) and the presence of neuromuscular syndromes associated with critical illnesses: critical illness myopathy and polyneuropathy [6, 8, 11–13]. Peripheral muscle weakness has been reported in 25–33% of patients undergoing MV for 4 to 7 days and in 60% of patients with respiratory failure [14, 15].

In light of these facts, interventions that encourage greater mobility in and out of bed during hospitalization are necessary to avoid or minimize losses associated with immobility and inactivity. The European Respiratory Society and the European Society of Intensive Care recommend starting these interventions as early as possible in critical patients, which can be done through both passive and active exercises [16]. Recent studies have indicated that early activity for ICU patients is safe and feasible, and results in a larger number of patients who leave the ICU functionally independent. Of all patients discharged from the ICU, those who underwent early mobilization left with fewer complications related to immobility and with improved functionality [17–19].

Among the benefits described in the academic literature on early mobility are increased days free of MV, reduced incidence of ventilator-associated pneumonia, reduced skin lesions, reduced days of hospital and ICU stay, decreased duration of delirium, and improved physical function at hospital discharge [5, 17, 19, 20].

There is no clear consensus on the ideal prescription for patients in ICU; however, the American College of Sports Medicine proposes a basic program [21]. The program should include a prescription of intensity, volume, and frequency for each patient to optimize the benefits from physical activity, even for ICU patients and those with respiratory insufficiency [7]. However, there are no guides or well-established practices for early and progressive mobility in the ICU. Determining the optimal initiation and progression of physical exercises can enhance beneficial effects of the protocol. Studies of current mobility protocols are still scarce in the academic literature of physical activity.

Rehabilitation programs within the ICU have been proposed, but the academic literature describes some limitations to early mobility in critical patients such as a lack of knowledge among professionals about early mobility, sedation practices, and insufficient numbers of professionals or equipment [5, 22]. Since a shortfall of professionals and a lack of equipment are cited as barriers to rehabilitation programs, the use of technology has emerged as a possible way to provide such services. Thus, the introduction of rehabilitation technologies, such as equipment for strength exercises, neuromuscular electrical stimulation, cycle ergometers, and equipment for walking can be an important factor in improving muscle strength, cardiopulmonary function, and functionality for patients in intensive care. Virtual reality has been suggested as a tool to improve certain cognitive functions. This is because exercise linked to virtual reality is able to offer demands that include multitasking, inhibition, taskswitching, short-term/working memory, and intelligence. Games can offer cognitive work since they generate cognitive demands such as: plan movements in order to hit targets, response inhibition, divide attention between tasks, sustain attention, follow visual and auditory cues, identify stimulus and decide quickly [23]. In the ICU, the use of these technologies, along with mobility programs, requires a thorough evaluation of the potential benefits and the safety, practicality, and efficacy.

Therefore, we created an early and progressive mobilization program based in four areas—muscle, cardiovascular, respiratory, and cognitive activities—to promote appropriate functional capacity and performance. The program includes exercises to maintain or recover basic function and to integrate these systems, preserving or recovering patients’ functionality even during hospitalization in the ICU.

The study’s hypothesis is that a progressive mobilization protocol and the use of technology is superior to conventional physiotherapy in promoting activity levels in the ICU and provides greater functional capacity at ICU discharge. Given evidence that points to the benefits of early mobilization, we chose to use conventional physiotherapy with the control group.

## Methods

### Aim

The primary goal of the study will be to compare the functional discharge status of ICU patients who undergo conventional physiotherapy with ICU patients who receive the progressive mobilization protocol. A secondary goal will be to assess and compare levels of physical activity in the ICU, length of stay, and pulmonary and muscle changes in patients who receive conventional physiotherapy and those who undergo the progressive mobilization protocol.

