#### Intervention group

The intervention group will undergo a program of early and progressive mobilization (Fig. 1) created by the research team, based on data in the academic literature. As maintenance of functionality seems to depend primarily on the muscular and cardiorespiratory systems, the program is designed for rehabilitation focused on these systems. The protocol describes exercises, techniques, and apparatus for maintenance of muscle length, maintenance and gain of muscle strength, aerobic exercises, exercises aimed at reeducation of gait, and cognitive components.

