#### Choice of activity level and criteria for progression in the mobilization program

The program consists of different levels of mobilization with progressive levels of activity, intensity, and types of exercise. To determine the appropriate level, the methods used to determine the appropriate level for each patient will be the patient’s ability to understand and their MS. The patient’s capacity to understand will be evaluated through requests to follow simple commands, such as “Put your hand on your head, bend your legs, open and close your eyes.” MS at the beginning of the program will be assessed using the MRC Strength Scale. A score of 3 points will be used as a cut-off to determine whether the patient can perform the movement alone and against the action of gravity. Patients capable of these movements will progress to the next level.

Thus, if a patient meets the criteria to enter the program, the next step will be to determine the activity level at which he or she will start the protocol. The first criterion is whether the patient can respond to commands; patients who are unresponsive will enter the program at level I. Patients who can follow commands will begin at levels II, III, IV, or V. To determine the specific level of each patient, MS is measured, with a cut-off score of 3 on the force scale. Patients with MS less than 3 will begins the program at level II, patients with MS of 3 or greater will begin at level III. The difference between level I and the other levels is the ability to understand commands, and the differences between the other levels depend on MS. After completing a level, the patient can move to the next level.

Patients will be reassessed daily to determine whether they can advance to the next level. To progress from level I to level II, the patient should have improved consciousness and be able to respond to commands. If MS is less than 3, the patient will enter level II. If the patient’s MS is equal to or greater than 3, they can advance directly to level III.

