#### Patient assessment procedures

At the time of admission to the ICU and up to 2 days after admission, the patient will be examined against the inclusion criteria. The patient’s functionality in the 2 weeks before admission will be evaluated with the Barthel Index, which will be assessed by directly questioning the patient or their caregiver if they are unable to respond. Evaluation will include hemodynamic, respiratory, and cardiac stability for the safe practice of early mobility, and the absence of exclusion criteria will also be assessed. The patient will then be randomly placed in the control group or the intervention group.

After the patient is enrolled in the study, the initial variables will be collected, consisting of data related to the patient and their hospitalized and pre-hospitalization levels of functionality. At that time, an accelerometer will be placed on the patient to monitor their level of physical activity during the entire stay in the ICU.

Data on the patient’s hospitalization and the evolution of their condition, as well as the level of physical activity performed, will be collected during the entire stay in the hospital.

Upon discharge from the ICU or within 2 days of discharge, all patients will undergo a complete evaluation of their respiratory, muscular, and functional systems through methods already described in the academic literature and performed by a blind evaluator. The accelerometer will be removed, and the data will be analyzed in a dedicated computer program. Figure 2 shows a flowchart presenting the methods used in the study.

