**Fig. 2 Fig2:**
[figure not shown]
Flowchart of the study

Patients in both groups will use an Actigraph wGT3X-BT accelerometer (ActiGraph LLC®, Pensacola, FL, USA) throughout the length of their hospital stay, a tool which analyzes their position and level of activity. The accelerometer will be placed on the dominant lower limb using a bandage and will not be removed until discharge, allowing information on the patient’s physical activity to be collected objectively. The evaluation of the intensity of the exercises performed during ICU stay in both groups will be performed through the parameters evaluated by the accelerometer. This instrument is able to identify the intensity of the exercise performed, and for analysis we will divide it into mild, moderate and intense or absence of activity. Exercise intensity will also be monitored and evaluated by the Borg Scale at the end of each physical therapy session. At the end of the ICU stay, the equipment will provide data such as the exercise intensity and time spent lying down, sitting, and standing [24].

The following data concerning hospitalization will be collected: use of vasoactive drugs, use of corticoids or neuromuscular blockers, hypoglycemia, the presence of sepsis, surgery, hemodialysis, use of invasive and non-invasive MV, tracheostomy, and the number of days spent in the different therapies that were evaluated.

Evaluation of the respiratory system, muscular system, and functionality after ICU discharge will be performed by a blind evaluator using methods previously described in the academic literature. These data will be correlated with the physical activity data obtained from the accelerometer.

The respiratory evaluation will be performed using the maximal inspiratory pressure test with the use of a manovacuometer (Wika Corporate®, Klingenberg, Germany), while evaluation of pulmonary function will be done through spirometry, assessing the forced expiratory volume in 1 second (FEV_1_) and maximum voluntary ventilation [25] with a Datospir – Micro C digital spirometer (Sibelmed®, Barcelona, Spain).

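### The secondary aim compares pulmonary and muscle changes, but the text schedules these tests once, at ICU discharge, so only discharge levels can be compared; starting strength is described for the intervention programme alone

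*Protocol article*

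**What the plan says.** **Objective.** The protocol article, Aim, lists among the secondary goals a comparison of "pulmonary and muscle changes in patients who receive conventional physiotherapy and those who undergo the progressive mobilization protocol". The abstract's Background words the same interest differently, as "the degree of pulmonary and muscle function, and the length of stay to analyze correlations between these variables".

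**Timing of the tests.** Abstract, Methods: "Evaluations will be made within 2 days of ICU discharge except for the level of activity, which will be evaluated daily". Patient assessment procedures: "Upon discharge from the ICU or within 2 days of discharge, all patients will undergo a complete evaluation of their respiratory, muscular, and functional systems". The same section, after the flowchart: "Evaluation of the respiratory system, muscular system, and functionality after ICU discharge will be performed by a blind evaluator".

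**Starting data.** After enrolment, "the initial variables will be collected, consisting of data related to the patient and their hospitalized and pre-hospitalization levels of functionality". No spirometry, respiratory pressure, handgrip or electromyography is named there. Under Primary and secondary outcome measures, a baseline-to-final difference is defined for the Barthel Index and the IMS only. The respiratory and muscular variables are listed without one.

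**Starting strength.** In the section on choice of activity level: "MS at the beginning of the program will be assessed using the MRC Strength Scale". Its stated use is to place the patient at a level. That programme belongs to one arm: "The intervention group will undergo a program of early and progressive mobilization". Under Control group, the unit physiotherapist has no access to it.

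**Eligibility.** Participants requires a Barthel Index of 100 before hospitalisation.

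**The concern.** A comparison of changes needs a starting and a final value on the same scale. The text supplies only the final one for the lung and muscle tests. If the report speaks of change, or of a patient's function having been preserved, it will claim something the data cannot show.

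The second issue is what describes a patient's condition at randomisation. Programme entry runs from patients unresponsive to commands to patients with MRC strength of 3 or more. That spread plausibly predicts discharge Barthel, IMS and handgrip. With 48 per arm, chance imbalance in it is possible. The pre-hospital Barthel Index is constant by design and cannot reveal it, and MRC strength is described for the intervention programme only. What remains for both arms is a baseline IMS or in-hospital functionality value. It is implied by the outcome definition and by the list of initial variables, but no section says when it is scored. Without a well-defined starting measure, the primary and muscle comparisons lose a check on balance and some precision.

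**Working it through.** **1. Schedule, measure by measure**

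| Measure | Starting value in the text | Discharge value |
|---|---|---|
| Maximal inspiratory and expiratory pressures | none stated | one |
| FEV1, maximum voluntary ventilation | none stated | one |
| Handgrip | none stated | one |
| Electromyography | none stated | one |
| Timed Up and Go, 2-Minute Walk | none stated | one |
| MRC strength | described for setting the programme level | none stated |
| Barthel Index | pre-hospital, 100 for all | yes |
| IMS | implied by the outcome definition, timing not given | yes |

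A within-patient change cannot be formed for any pulmonary or muscle test. MRC cannot stand in as the starting value for handgrip, because it is a different instrument.

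**2. The plan's own sample size.** Inputs from the statistical section: difference 13, SD 22, 80% power, 48 per group. The printed alpha is 0.5. I read it as two-sided 0.05, because 0.5 would give only 14 per group. Normal approximation: n = 2(1.960 + 0.842)² × 22² / 13² = 45 per group after rounding up. The t test gives 46. The stated 48 is slightly larger, and t-test power at 48 is 81.7%.

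**3. Value of a starting covariate for the Barthel comparison.** The correlation r between starting state and discharge score is not in the document, so I assume 0.3 to 0.5. Adjustment removes a share r² of the variance, 9% to 25%. Residual SD = 22√(1 − r²), with 48 per group:

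| r | Residual SD | Power |
|---|---|---|
| 0 | 22.0 | 81.7% |
| 0.3 | 21.0 | 85.2% |
| 0.4 | 20.2 | 87.8% |
| 0.5 | 19.1 | 91.1% |

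**4. Why a missing-value category would do harm.** The trial has recruited since February 2017, is due to finish in July or August 2018, and was published in May 2018. Under uniform accrual (assumed), about 40 of 48 controls would already be enrolled. If they have no MRC value, a missing category would hold controls only. With an indicator for each category, those patients add nothing to the treatment contrast. Power with 48 intervention patients against the controls left, using SE = residual SD × √(1/48 + 1/n of controls):

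| Controls with a value | r = 0.3 | r = 0.5 |
|---|---|---|
| 8 | 36% | 42% |
| 24 | 69% | 77% |

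All four figures lie below the unadjusted 81.7%.

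**The case against.** The strongest reply is that one word is loose and the plan is otherwise coherent. The article's Background section uses changes in the sense of alterations, the abstract speaks of degree of function, and every timing statement points to discharge. This is plausible, and it is why rewording is enough for the objective. The Aim and the schedule still have to say the same thing.

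The second reply is that randomisation makes discharge values comparable without a baseline. This stands in full. Discharge-only testing is also defensible because some patients enter unresponsive and could not perform voluntary spirometry or handgrip.

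The third reply is that the article is condensed. The flowchart and the schedule figure are not shown, and covariate adjustment is often left to an analysis plan. This limits what can be said about controls: that they receive no MRC test is an inference from silence, not something the article states. It does not remove the mismatch between the objective and the three timing statements, which agree with one another.

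The fourth reply is that the power gain concerns a primary comparison already above its 80% target. That is correct, so the gain is optional efficiency.

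**Conclusion.** The point holds in a limited form. As the text stands, no within-patient change in lung or muscle function can be computed in either arm, and the secondary objective should not promise one. The consequence is one of wording and interpretation, plus a modest loss of precision: about 82% power without adjustment against 85–91% with it. Those figures rest on an assumed correlation of 0.3 to 0.5 and on alpha read as two-sided 0.05.

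Two stronger readings are tempting and are not supported. A reader might infer that the trial can say nothing about whether the programme improved lung or muscle function. In fact a difference between randomised arms at discharge estimates the effect relative to conventional physiotherapy without bias. A reader might also infer that starting imbalance can be neither seen nor adjusted for. The initial variables and the primary outcome definition imply a baseline IMS or in-hospital functionality value in both arms. It measures mobility rather than strength and its timing is not fixed, but it is a usable starting measure.

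**What to change.** 1. Restate the secondary objective in the Aim as a between-arm comparison of pulmonary and muscle function at ICU discharge, with no claim of within-patient change. This costs a sentence.

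2. From now on, score the starting state of every patient in both arms before the envelope is opened: command response, MRC category (unresponsive, below 3, 3 or above) and baseline IMS. Name it as a prespecified covariate for the Barthel, IMS and muscle outcomes. This costs a few minutes of bedside testing per control patient and needs no new equipment.

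3. For patients already enrolled, adjust only for a baseline value available in both arms, such as the baseline IMS. Do not use a missing-MRC category that would contain only controls. If MRC exists for later patients only, report it descriptively.
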